# Duramesh™ versus conventional suture for prevention of trocar-site hernia following laparoscopic surgery (TROCAR): study protocol for a double-blind randomised controlled trial

**DOI:** 10.1186/s13063-025-09388-3

**Published:** 2025-12-30

**Keywords:** Duramesh, Mesh suture, Trocar-site hernia, Hernia prevention, Laparoscopic surgery

## Abstract

**Background:**

Trocar-site hernia is an underappreciated condition with estimates of approximately 25% at 2 years follow-up. Duramesh™ has emerged as a novel product with potential benefits for incisional hernia prevention. The aim of this trial is to establish if Duramesh is superior to conventional suture for prevention of periumbilical trocar-site hernia following laparoscopic surgery.

**Methods:**

The TROCAR trial is a prospective single-centre, parallel arm, double-blind randomised controlled trial conducted in the United Kingdom. A total of 250 randomised participants (1:1 ratio) will be allocated to receive either Duramesh or conventional suture (J-vicryl or J-PDS). The primary outcome is the cumulative incidence of sonographically detected periumbilical trocar-site hernia at 2 years of the index operation. Secondary outcomes are 90-day surgical site occurrence (SSO), 90-day surgical site infection (SSI), 90-day rate of reoperation, 90-day mortality, length of hospital stay, and quality of life at 3 months, 1 year and 2 years measured using a modified EuraHS-QoL score and modified Carolinas Comfort Scale.

**Conclusion:**

TROCAR will provide level 1 evidence on trocar-site hernia prevention in both the emergency and elective settings.

**Trial registration:**

Registration number ISRCTN14473961 (https://doi.org/10.1186/ISRCTN14473961). Registered on 14th April 2025.

**Supplementary Information:**

The online version contains supplementary material available at 10.1186/s13063-025-09388-3.

## Background

During laparoscopic surgery, ports or trocars are inserted into the abdominopelvic cavity to facilitate gas insufflation and access for surgical instruments. Entry into the abdominopelvic cavity typically commences around the umbilicus as postoperative scars are relatively well hidden and the cicatrix can be lifted to reduce the risk of enterotomy. A small incision at the base of the cicatrix and through the adjoining linea alba is required. However, this predisposes to trocar-site incisional hernia (or trocar-site hernia (TSH)) where intraabdominal viscera or fat protrudes through the surgical defect after closure [1]. TSH occurrence is higher when incisions are larger, such as those 10 mm and greater, or extended as a specimen extraction site [2]. TSH are therefore felt to occur more commonly at the periumbilical region as this is conventionally where larger 10 to 12 mm trocars are placed for laparoscopic camera access [1].

There is considerable variation in the reported incidence of TSH from 0 to 39% [3]. A survey of American surgeons found that the perceived rate of TSH for trocar sites 10 mm and above was 5% [3]. However, this is likely an underestimate as much of the available literature consists of retrospective studies with poorly defined follow-up, inadequate follow-up duration and insensitive hernia assessment (for example, using palpation or self-reporting rather than imaging confirmation) [4]. Imaging is known to increase the diagnostic yield as clinically occult herniae are detected [5, 6]. High-quality prospective studies, including those with longer follow-up duration and imaging confirmation, have found the incidence to exceed 25% [7–9].

Periumbilical trocar site closure is usually performed with slowly absorbable suture such as vicryl or polydioxanone (PDS). Most surgeons do not perform a concurrent repair with prophylactic planar mesh as implantation prolongs surgery and developing a retromuscular plane (considered the gold standard for mesh placement) without extending the fascial incision is technically challenging. Some authors investigated prophylactic mesh implantation during laparoscopic surgery but utilised onlay repair [4], which was ineffective for preventing TSH compared to suture closure alone. Alternative options have been explored such as intraperitoneal mesh, but there are concerns this may precipitate adhesions to viscera and enterocutaneous fistulae [10]. A simple solution to prevent TSH is needed, especially since minimally invasive surgery is now the standard of care for many operations.

### Duramesh™

Duramesh is a novel product that combines properties of conventional suture with planar mesh. It gained its Conformité Européenne (CE) mark in May 2021 and United States Food and Drug Administration (FDA) approval in September 2022 and thereafter has been clinically indicated for cases of abdominal wall closure and ventral hernia repair. Specifically, in contrast to conventional suture, which has a single filament, Duramesh comprises multiple filaments that form a permeable cylindrical shape in cross-section. It is implanted and tied in a similar manner to conventional suture, but flattens when tension is applied, at which point it resembles a ribbon of planar mesh.

The mechanism of action of Duramesh is thought to be due to the distribution of tension at the suture tissue interface [11]. This limits the effect of ‘cheesewiring’ which can create defects in tissue that enlarge over time with repeated abdominal wall straining. Duramesh has shown greater resistance to tissue pull-through compared to conventional suture in pre-clinical models [12], and a recent systematic review [13] suggests it may be associated with low rates of incisional hernia at 12 months (median 3.4%, *n* = 553). We aim to perform a prospective comparative study investigating the effectiveness of Duramesh for closing laparoscopic periumbilical trocar sites.

## Methods

### Study design

TROCAR is a single-centre, parallel arm, double-blind randomised controlled trial. The study objective is to assess whether Duramesh is superior to conventional slowly absorbable suture (also known as J-vicryl or J-PDS) for closing laparoscopic periumbilical trocar sites 10 mm or greater.

### Setting

The Sponsor and study centre is Croydon University Hospital, a university affiliated district general hospital in London, part of the National Health Service, United Kingdom (UK). Ten consultant surgeons and two associate specialists will be randomising patients and performing closure of the periumbilical trocar site. Their collective practice includes approximately 750 patients, who undergo laparoscopic surgery annually.

### Primary outcome

The primary endpoint is the cumulative occurrence of trocar-site hernia (TSH) over 2 years following the index operation. For this trial, TSH is defined as an ultrasound-detected fascial defect of 10 mm or greater within the vicinity of the periumbilical scar, with or without protrusion of intraabdominal or pre-peritoneal contents, and with or without symptoms.

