### Participant timeline (Table 1) and baseline data

**Table 1 Tab1:**
[figure not shown]
Scheduled and unscheduled visits with timepoints for data collection

Data will be recorded using electronic case report forms (eCRFs) on a secure web-based system (Project REDCap, Vanderbilt University, TN, USA). These consist of baseline demographics, medical history, treatment group, operative details, and primary and secondary outcomes. Follow-up timepoints are 3 months, 1 year and 2 years after the index operation. Additionally, patients requiring inpatient admission will be reviewed by a researcher before discharge for wound events as defined previously.

Baseline demographic data includes age, gender, smoking status, and previous abdominal surgery. Medical history includes history of diabetes, active malignancy, medications affecting healing (chemotherapy, steroids, biologics), ASA grade and comorbidities. Operative details include responsible consultant, pre-operative antibiotics, laparoscopic operation, length of procedure, CDC wound classification, and material used for skin closure.

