### Three-month follow-up

Participants are contacted by telephone to arrange a suitable time to visit the outpatient clinic. Information gathered will include length of hospital stay, readmissions within 90 days, return to theatre within 90 days, SSO within 90 days and QoL using modified versions of validated questionnaires. Furthermore, participants will have physical and ultrasound examinations performed by a trained sonographer for the presence of TSH. In this trial, imaging is the definitive modality for detecting the primary outcome. The precise extent (in mm) of any defect, if present, will be recorded, as will whether there is any hernia through this. If so, the width and craniocaudal diameter of the hernia sac will be recorded, along with the presence of any content beyond fat.

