### One-year and 2-year follow-up

Data collected at these timepoints are QoL scores and presence of TSH. Ultrasound examination will be performed by the same sonographers who remain blinded to the participant treatment arm. Patients with confirmed TSH detected before the primary endpoint of 2 years are offered ongoing follow-up to monitor TSH size and continued QoL assessment.

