### Adverse event reporting

In this trial, adverse events (AE) are defined as any untoward medical occurrence in a subject to whom an intervention has been administered, including occurrences which are not necessarily caused by or related to the intervention and that exceed grade 1 of the Clavien-Dindo classification [24]. Serious adverse events (SAE) are defined as events which result in death, are life-threatening, require or prolong hospitalisation, or result in significant disability/incapacity. However, the following exceptions are already defined in this protocol and so will not be recorded as an adverse event; these are trocar-site hernia which will be assessed as a primary outcome, and wound events defined under SSO will be assessed as a secondary outcome.

We do not anticipate any device-specific AEs or SAEs. Suture granuloma and chronic draining sinuses are theoretically more common with non-absorbable suture material, but the largest published series of Duramesh implantation suggests these are rare, with an incidence of 0% and 0.3%, respectively [25]. Both will be reported as secondary outcomes, as stated above. AEs and SAEs will be reported unsolicited, and their relationship to the treatment arm graded as either unrelated, possible, probable or causal. Patients admitted to the hospital after their operation are reviewed daily by blinded outcome assessors for AEs, SAEs and wound events. Following discharge, trial participants are asked to inform the trial coordinator if they re-present to the hospital, whether that be related or unrelated to the index operation. Participants are also asked to contact the trial coordinator if they have any health-related concern so that AEs or SAEs are not missed.

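### The cumulative 2-year primary endpoint has no route for a trocar-site hernia confirmed on CT or at operation, so one repaired between scans could be lost

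*Protocol article*

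**What the plan says.** The Primary outcome section makes the endpoint cumulative: "The primary endpoint is the cumulative occurrence of trocar-site hernia (TSH) over 2 years following the index operation". It then fixes what counts: "For this trial, TSH is defined as an ultrasound-detected fascial defect" of at least 10 mm near the periumbilical scar, whether or not there is protrusion or symptoms. The Three-month follow-up section adds: "In this trial, imaging is the definitive modality for detecting the primary outcome". Scan times follow the visit schedule: "Follow-up timepoints are 3 months, 1 year and 2 years after the index operation".

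Other sections bear on whether a hernia found outside a trial scan would be recorded:

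- **Adverse event reporting** exempts from adverse event recording "trocar-site hernia which will be assessed as a primary outcome". It also asks participants to tell the trial coordinator about any return to hospital or health concern.
- **Secondary outcomes** limits reoperation to 90 days.
- **One-year and 2-year follow-up** states: "Data collected at these timepoints are QoL scores and presence of TSH". It treats a hernia confirmed before 2 years as such and offers continued follow-up.
- **Table 1** is captioned "Scheduled and unscheduled visits with timepoints for data collection"; its content is not shown.
- **Statistical methods** omits missing values from the primary analysis and uses multiple imputation in a sensitivity analysis.

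**The concern.** A cumulative endpoint should count every hernia that occurs within 2 years. This definition counts only those that an ultrasound has seen. The gaps between scheduled scans are 9 months (month 3 to month 12) and 12 months (month 12 to month 24). The Discussion itself names bowel incarceration as a consequence of trocar-site hernia. A hernia that presents acutely may be diagnosed by CT or at operation and repaired before the next trial scan. Scanning an intact repair would then show no defect.

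The hernias at risk of being lost are those serious enough to need repair, while an occult 10 mm defect without symptoms counts in full. The Discussion concedes that the clinical relevance of occult hernias is debatable, which makes this asymmetry harder to defend. If Duramesh prevents hernias, more of the lost events would be expected in the control arm, which would shrink the observed difference and cost power.

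**Working it through.** **Step 1. What happens to such a case under the stated rules**

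| Course of the hernia | Result on a literal reading |
|---|---|
| Seen at a trial scan, then repaired | Event (endpoint is cumulative) |
| Diagnostic ultrasound shows a defect of at least 10 mm before repair | Can qualify; the definition is not limited to scheduled scans |
| CT or operative diagnosis, repaired, later trial scan negative | No event |
| CT or operative diagnosis, repaired, no later trial scan | Missing, omitted from the primary analysis |

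The problem is confined to the last two rows.

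**Step 2. Whether the described data would recover it**

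- The adverse event exemption closes one route, on the ground that the primary outcome covers hernia. In the last two rows it does not.
- Reoperation as an outcome ends at 90 days, about when the first long gap begins.
- The items named for 1 and 2 years are quality of life and presence of hernia; a repair since the last visit is not named.
- Return to hospital is reported by the participant, and no section links that report to the endpoint.

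**Step 3. Reproduce the plan's sample size**

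Inputs from the Sample size section: p1 = 0.25, p2 = 0.10, alpha 5%, power 80%. Two-sided testing is from Statistical methods and 1:1 allocation from the Abstract. With pooled variance under the null and p̄ = 0.175:

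n = [1.960 × √(2 × 0.175 × 0.825) + 0.842 × √(0.25 × 0.75 + 0.10 × 0.90)]² / 0.15² = 99.5, so 100 per group.

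200 / 0.80 = 250. Both stated figures reproduce. Power at n = 100 is Φ[(d√n − 1.960√(2p̄(1 − p̄))) / √(p1(1 − p1) + p2(1 − p2))] = Φ[(1.500 − 1.053) / 0.527] = Φ(0.848) = 80.2%.

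**Step 4. Illustrate the loss**

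The documents give no rate of repair without a qualifying ultrasound. Assume a share m of true hernias is lost equally in both arms and scored as no event. The observed rates are then 0.25(1 − m) and 0.10(1 − m).

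| m (assumed) | Control | Duramesh | Difference (points) | Power, 100 per group |
|---|---|---|---|---|
| 0 | 25.0% | 10.0% | 15.0 | 80.2% |
| 2% | 24.5% | 9.8% | 14.7 | 79.2% |
| 5% | 23.75% | 9.5% | 14.25 | 77.7% |
| 10% | 22.5% | 9.0% | 13.5 | 74.9% |

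At m = 10% this is 2.5 control and 1 Duramesh participants per 100.

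If the same cases were missing instead, the observed rates would be p(1 − m)/(1 − pm). At m = 10% that is 0.225/0.975 = 23.1% against 0.09/0.99 = 9.1%, a difference of 14.0 points and power of 76.5%. The loss is smaller but goes the same way.

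**Step 5. Direction**

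With unequal shares scored as no event, the observed difference is 0.15 − 0.25·m(control) + 0.10·m(Duramesh). It shrinks unless the missed share with Duramesh is more than 2.5 times that in control.

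**The case against.** The strongest reply is that the gap is narrow. The endpoint is cumulative, so an earlier positive scan is not undone by repair, and a diagnostic ultrasound outside the schedule could qualify. This is correct, and the point is limited accordingly.

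A reader might infer that every hernia repaired between scans is scored as no hernia. The documents do not say so. That result follows from the definition only for a hernia without a qualifying ultrasound and with a later negative scan; without a later scan the outcome is missing.

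A reader might also infer that nothing else could capture such a case. That goes too far. Participants are asked to report any return to hospital, with no 90-day limit, and Table 1 covers unscheduled visits that cannot be seen here. What stands is that no section shown feeds either source into the endpoint. Nor does the adverse event exemption decide how a case is scored; its stated purpose is to route hernias to the primary outcome.

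It can also be said that a condensed article leaves case handling to the full protocol, the case report form and the statistical analysis plan. That is fair for form items. It does not dispose of the definition, which the article states outright and which excludes these cases as worded. An analysis plan also cannot recover repairs that were never recorded.

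Finally, the power figures rest on assumptions. A much larger loss can be produced: 4% of control and 1% of Duramesh participants gives 21% against 9% and power of 66.4%. That requires 4/25 = 16% of control hernias and 1/10 = 10% of Duramesh hernias to be repaired without a qualifying scan. Nothing in the documents supports such rates, and the endpoint includes small defects without symptoms.

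**Conclusion.** The concern holds in limited form. The primary endpoint is cumulative, but its definition has no route for a periumbilical trocar-site hernia first confirmed on CT or at operation. A hernia that arises and is repaired between scans without a qualifying ultrasound could be scored as no event or dropped as missing, and the data collection described does not secure its capture.

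The size is unknown. Under an assumed equal missed share of 2% to 10% scored as no event, power falls from 80.2% to between 79.2% and 74.9%, and the observed difference from 15 to between 14.7 and 13.5 points. The sample size is not in error. The cost in power is probably modest. The main reason to act is that the endpoint may omit the most clinically important hernias, and that this is cheap to correct.

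**What to change.** Make three changes.

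1. Amend the definition in the Primary outcome section. Trocar-site hernia should also include a periumbilical trocar-site hernia confirmed by clinical imaging or at operation, including any repair, within 2 years of the index operation. The blinded radiologist already named as adjudicator should decide these cases from reports with the closure material redacted.
2. At the 1- and 2-year visits, record any periumbilical hernia diagnosis or repair since the last visit, and check it against hospital records.
3. Report ultrasound-only trocar-site hernia as a sensitivity analysis.

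The cost is one sentence in the definition, one item at existing visits, and the record check. A few events would rest on clinical records and may lack a measured 10 mm defect. Redaction is essential because an operative report may reveal the material, and the Blinding section keeps operating surgeons out of outcome data collection for that reason. Recruitment began in June 2025, so no participant reaches 2 years before June 2027 and there is time to amend.

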### Secondary outcomes

These include:Incidence of periumbilical surgical site infection (SSI) within 90 days, categorised by the Centers for Disease Control and Prevention (CDC) [14] as superficial, deep and organ-space.Incidence of periumbilical surgical site occurrence (SSO) within 90 days, categorised by the Ventral Hernia Working Group (VHWG) [15] as SSI, seroma, haematoma, superficial dehiscence, fascial dehiscence, enterocutaneous fistula, suture granuloma and chronic sinus tract.Reoperation within 90 days of the index operation.Length of hospital stay.Mortality within 90 days of the index operation.Measurement of postoperative quality of life (QoL) using modified versions of validated questionnaires – EuraHS-QoL score [16] and Carolinas Comfort Scale (CCS) [17, 18].

### Eligibility criteria

Inclusion criteria are adults 18 or older; able to provide informed consent without barriers that might prevent follow-up; and any laparoscopic procedure requiring periumbilical incision for trocar insertion ≥ 10 mm, elective or emergency, pertaining to the domain of general surgery. Acceptable situations include extraction sites up to a maximum of 3 cm, concurrent umbilical hernia if the defect is small enough to accommodate the camera port, and previous abdominal surgery except for the condition specified in the exclusion criteria below.

Exclusion criteria at screening are lack of capacity to provide informed consent; planned open operation; procedures where placement of periumbilical trocar < 10 mm is planned; periumbilical trocar insertion not planned or not possible; specimen extraction site at the umbilicus exceeds 3 cm; use of planar mesh to cover the periumbilical trocar site; previous planar mesh covering the periumbilical trocar site; previous abdominal surgery, if in the opinion of the Principal Investigator, is not suitable for inclusion, e.g. ‘battlefield’ abdomen, enterocutaneous fistulae, multiple previous laparotomies etc.; CDC wound class 4; pregnancy; and body mass index (BMI) ≥ 40.

For elective and expedited surgery, patients fulfilling inclusion criteria and not meeting exclusion criteria will be offered the opportunity to participate in advance by researchers screening operating lists. Patients undergoing emergency surgery will be offered the opportunity to participate by the consultant surgeon on call when the decision for laparoscopic surgery is declared.

### Standardisation

Training sessions for participating surgeons were conducted to facilitate standardisation of technique when entering and closing the abdomen. An open Hasson cut-down approach and a vertical midline incision in the linea alba are mandated. Fascial stay sutures are permitted but must not contribute to the final fascial closure. Once the operation is complete, closure will be performed with a series of simple interrupted sutures. The number of simple interrupted sutures required will depend on the size of the incision, as some incisions will need to be extended to extract the specimen (up to a maximum of 3 cm). As a result, the midline incision will be closed vertically. Other than the closure method, there is no difference in perioperative management between intervention and control groups.

### Intervention arm

These patients will have interrupted closure with size 1 Duramesh on a 26 mm needle, product code MSP300-5. The number of interrupted sutures along the length of the wound, required to achieve a robust closure, will be at the discretion of the operating surgeon, but bites are recommended to be taken approximately 8 mm from the fascial edge and approximately 8 mm apart. The number of throws required to secure each Duramesh stitch should be exactly 5. After each final throw, the knot should be pulled and pressed down by the operating surgeon, adding a little extra force to the mesh suture ends. The knot may be buried at the surgeon’s discretion in low BMI participants or if there are concerns about a suture granuloma or chronic sinus tract. This is performed by taking a further bite into the subcutaneous fat to invert the knot away from the skin surface. The ears of the knot should be cut to approximately 3 to 4 mm in length, as recommended by the manufacturer. The skin is closed according to surgeon preference. An adhesive dressing or skin glue will be applied over this, again according to surgeon preference.

